# Community reinforcement and family training (CRAFT) - design of a cluster randomized controlled trial comparing individual, group and self-help interventions

**DOI:** 10.1186/s12889-019-6632-5

**Published:** 2019-03-14

**Keywords:** Community reinforcement and family training, CRAFT, Concerned significant others, Alcohol treatment, Treatment engagement, Alcohol use disorder

## Abstract

**Background:**

Around 585,000 people in Denmark engage in harmful use of alcohol with 140,000 suffering from outright alcohol dependence. The concerned significant others (CSOs) are affected by the drinking, often suffering almost as much as the person with alcohol use disorder. Community Reinforcement and Family Training (CRAFT) is aimed at CSOs who struggle unsuccessfully, in an effort to motivate their loved ones to stop drinking and seek treatment. The aims of this study are 1) To implement CRAFT interventions into the daily routine of operating Danish alcohol treatment centers 2) To investigate whether 6-week-individual CRAFT, 6-week-open group-based CRAFT or CRAFT based on self-help material, is efficient in getting problem drinkers to seek treatment for their alcohol problems 3) To investigate which of the three interventions (individual, group or self-directed CRAFT) is the most effective and in which group of population.

**Methods:**

The study is a three-arm, cluster randomized controlled trial: A: individual CRAFT, group CRAFT, and CRAFT as a self-help intervention. A total of 405 concerned significant others to persons with alcohol abuse will be recruited from 24 alcohol outpatient clinics. The participants will fill out a questionnaire regarding i.e. life quality, if the drinking person entered treatment (main outcome) and satisfaction with the intervention, at baseline and after 3 and 6 months.

**Discussion:**

We expect to establish evidence as to whether CRAFT is efficient in a Danish treatment setting and whether CRAFT is most effective at individual, group or self-help material only.

**Trial registration:**

Clinical trials.gov ID: NCT03281057. Registration date: September 13th, 2017.

## Background

It is estimated that 585,000 people in Denmark engage in harmful use of alcohol with 140,000 suffering from alcohol dependence [1]. However, only 15,000 [2] seek specialist treatment for their alcohol problem, often after they have been suffering from an alcohol use disorder (AUD) for more than 10 years [3]. In spite of the severe consequences of AUD, people with AUD (PWAUD) may not seek treatment for AUDs due to fear of subsequent stigma or being incapable of completing treatment [4], although the most commonly reported reason to not seek treatment is the belief that one should be able to deal with the drinking problem without outside help [5]. The concerned significant others (CSOs), such as spouses, parents, or adult children, are affected by the drinking, often suffering almost as much as the PWAUD him - or herself [6].

The populations of CSOs are silent populations. CSOs easily get caught up in a pattern of behaviour that is nothing short of destructive [7]. Studies have shown that CSOs suffer from symptoms such as anxiety, depression, stress, concentration difficulties, physical pain and anger because of a poor relationship with the PWAUD [8]. In addition, violence and sexual abuse are often linked to an alcohol problem [7, 9]. Indeed, compared to the general Danish population, the frequencies of such symptoms are two to three times more common both among persons with an AUD and among their partners [10, 11].

The CSO’s high degree of involvement in and focus on the state of a person with AUD in the family, may lead to the neglect of children in the family. It is estimated that 122,000 children in Denmark live in a family with drinking problems [12].

In the Danish National Health survey 2010 [13], heavy drinkers in the Region of South Denmark were asked where, if at all, they would seek help to reduce drinking. Most drinkers had no such desire, but were they to consider seeking help, the most common choice would be looking to family and friends, followed by the general practitioner. Choosing to seek specialist treatment ranked very low. For that reason, it makes excellent sense to empower the families and friends of the person suffering from an AUD, enabling them to act in ways that help PWAUDs towards seeking and receiving treatment.

### What kind of intervention is relevant for CSOs?

Five types of interventions, aimed at the CSOs, have been described: self-help groups (Al-Anon/Nar-Anon) which are part of the Minnesota treatment family [14], the Johnson Institute Intervention (a very confrontational approach) [15], general unspecific support (typically aimed at supporting the CSO only, but not addressing how to increase the likelihood of getting PWAUD into treatment) [16], The 5-step method [17] and Community Reinforcement and Family Training (CRAFT). So far, CRAFT is the only one of these methods with any evidence to support that it increases the likelihood of the PWAUD seeking treatment [18]. CRAFT was proposed in 1986 by Sisson and Azrin [19] aimed at training CSOs to become involved in the problem drinkers’ choice of treatment, helping CSOs handle situations between themselves and the problem drinkers, and finally helping the CSOs to develop specific strategies to take proper care of themselves in risk situations [20, 21].

### Craft

CRAFT is aimed at CSOs who struggle, unsuccessfully, to motivate their loved ones to stop drinking and seek treatment. CRAFT promotes active, positive participation from the CSOs in seeking to attract problem drinkers into treatment; changing CSOs’ efforts to help by developing their roles as active collaborators, supportive of the problem drinker. The underlying assumption of CRAFT is, that CSOs already have a detailed knowledge of the problem drinkers’ behaviour and that they are in a strong position to influence PWAUDs’ behaviour because of their concern and personal motivation, including getting PWAUDs to seek treatment [8]. So far, eight randomized or controlled clinical trials on CRAFT have been carried out on CSOs to alcohol dependents and drug users [16, 18–20, 22–25]. Three studies focus on alcohol problems [16, 19, 25], three studies on drug users [22–24], and two studies on both drug users and alcohol dependents [18, 20]. One of the studies on drug users studied CRAFT as a supplement to opioid-dependent adults already in treatment [24]. All studies have been carried out in the USA except one study on alcohol, which was carried out in Germany [25]. The German study compared CRAFT Immediate Intervention with waiting list and found a significantly higher engagement rate (B 1.34 SE 0.6) for the people receiving immediate intervention [25]. The American studies showed a two to three times higher impact in getting PWAUD to attend treatment after four to six CRAFT sessions with CSOs, compared with Al-Anon and Johnson Institute interventions [26]. In general, CRAFT interventions to CSOs lead to more than 60% of the PWAUDs in question to attending treatment in US [16]. Several of these studies have rather small samples from 12 to 40 CSOs [19, 20, 22] The original full intervention of CRAFT consists of 12–14 sessions [19]. Kirby et al. (2017) tested CRAFT in a four-six session intervention, where the only focus in the sessions was on Treatment Entry Training (TEnt) vs. the original CRAFT in 12–14 sessions and Al-Anon/Nar Anon (ANF), and 115 CSOs participated in the study. There was no counseling about e.g. relationship or substance use [18]. The treatment entry rate, after the intervention, was 62% for the CSOs randomized to the full CRAFT and 63% for the ones randomized to Tent, which was significantly higher than the ones receiving Al-Anon/Nar Anon (treatment entry rate 37%). This was to be expected, as the goal of Al-Anon/Nar-Anon is not to encourage treatment entry. No significant differences in mood and functioning were found between the three interventions, even though it was not a subject in the TEnt intervention.

CRAFT has, until now, been examined and shown effective in the USA and Germany. To our knowledge, studies on CRAFT have also been initiated in the Netherlands (ClinicalTrials.gov ID: NCT02510508) and Sweden (ISRCTN 38220020), but the results are not yet published. In the Netherlands researchers are performing a three-armed RCT with group, self-directed CRAFT or non-intervention addressed to CSOs to alcohol dependents. In Sweden, the effect of a five-week internet-based CRAFT program is tested versus waiting list (ISRCTN 38220020), in addition to another study on an online self-help program combined with a parent-training program for partners suffering from alcohol use disorder, versus a brief psycho-education program [27]. Moreover, a RCT study on CRAFT for CSOs with problem gamblers (CRAFT vs. treatment as usual) is currently being conducted in Sweden [28]. Earlier studies performed are based on small populations, and no study of CRAFT has been performed in Denmark so far.

Furthermore, to our knowledge, only one effectiveness study, performed in operating treatment institutions and as part of routine praxis, has been conducted [29]. The study from Dutcher et al., 2009, tested CRAFT in a community treatment center in the USA. Altogether 99 CSOs were concerned about alcohol abusers, whereas, for all CSOs, 55% of the treatment-refusing abusers entered treatment after 6 months. Among the CSOs, who completed at least four sessions on CRAFT, or the ones who engaged the abuser to treatment, 65% entered treatment. Further, effectiveness studies outside the USA are still essential before large-scale implementation.

The efficacy studies and the effectiveness studies performed, so far, indicate that CRAFT is effective for CSOs towards getting the drinking person into treatment and to improve the quality of life of the CSO and the relationship between the drinking person and the CSO [16, 18–20, 22–25]. Whether CRAFT delivered in group, individual or as self-help material is equally effective is, however, still unknown. The study of Manuel et al. indicated, that CRAFT in group condition may be just as effective as individual CRAFT, but the study was indeed small and did not compare the two settings directly. In the study of Manuel et al., 40 CSOs were randomized to either group CRAFT or self-directed CRAFT, and 60% of the CSOs in group CRAFT had their loved ones enter treatment, and for the self-directed CRAFT the result was 40% after six months [20]. Hence, the findings were promising, but not conclusive or significant.

Furthermore, groups can be organized as closed groups or open groups. In closed groups, all CSOs start at the same time and no new members are enrolled, once the treatment has begun. An open group can start when a minimum of two members are enrolled in the study and new members are included continually until the maximum of group members has been reached. When testing CRAFT in a closed group format, Manuel et al. experienced challenges with the start-up, because it took up to one month to gather enough CSOs to start a group [20]. Compared to closed groups, open groups can be joined without a waiting period. Furthermore, an open group format may create opportunities for senior members in the group to share experiences and advice with newcomers [20]. However, an open group format may also be negatively affected by a constant influx and outflux of people in the group, in addition to not all group members receiving the sessions in a logical order. A general strength of group therapy, in proportion to individual and self-help, may be that the CSOs meet like-minded individuals and are able to share similar experiences and feelings and support each other.

### Aim and hypotheses

The aim of this study is to implement CRAFT interventions into the daily routine of Danish community alcohol treatment centers, and investigate whether 6 week-individual CRAFT, 6 week-open group-based CRAFT or based on CRAFT self-help material only, is efficient in getting problem drinkers to seek treatment for their alcohol problems – and which of the three interventions (individual, group or self-directed CRAFT) is the most effective.

#### Hypotheses

1. CSOs, randomly assigned to either individual CRAFT or to open group CRAFT, will significantly more often be able to motivate their drinking relative to enter treatment compared to CSOs, randomly assigned to the control condition (self-directed CRAFT).

2. We hypothesize that six sessions of group CRAFT improve the quality of life and psychological functioning of CSOs significantly more than individual CRAFT and self-directed CRAFT.

## Methods

### Design

The study is a cluster randomized controlled trial, carried out in public alcohol treatment facilities. All public alcohol treatment centers in Denmark have been invited to participate in a partnership with the Unit of Clinical Alcohol Research at the University of Southern Denmark. In all, 61 institutions were invited to participate, and 17 institutions agreed to participate in the study. The treatment facilities have been randomized to offer one of the three following CRAFT formats:CRAFT as individual format, consisting of six individual sessions with a therapist and a self-help bookCRAFT in an open group format. The groups start when two CSOs have contacted the treatment facility and will then continuously include new members, consisting of six group sessions with one or two therapists, in addition to the participants also getting a self-help book.Control condition, consisting of CRAFT delivered in a self-directed format and using a self-help book only.

### Power calculation

Based on the data from Manuel et al. [20], we expect 40% of CSOs receiving self-help material and 60% of the CSOs receiving either Group CRAFT or Individual CRAFT to be able to motivate the drinkers to enter treatment. Furthermore, the effect of CRAFT is one-sided as the intervention of CRAFT cannot make the situation inferior for either the CSO or the drinker [8]. Based on these expectations, 106 participants in each group are needed to be able to detect a 20%-point difference with an α level at 5%, a power of 90% and an ICC of 0.05. As we foresee a dropout rate at approximately 10% and, furthermore, a loss to follow-ups rate at 10%, we need to include at least 135 CSOs in each group. This gives an expected total of 405 CSOs.

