### Ethics

In view of the fact that the CRAFT intervention has proven highly effective in the US, and since living close to a problem drinker is such a burden to the individual and, finally, because the Danish National Guidelines strongly recommend the implementation of CRAFT, we find it un-ethical and problematical not to offer CRAFT in some form to all the participants, even to the control condition. However, since we expect less effect of the control condition (CRAFT as self-help material), for ethical reasons, the participants in the control group will be offered an individual CRAFT session three month after enrollment. Training significant others in new communication strategies and new ways of acting, in relation to the problem drinker, may lead to increased tension in the family set-up. Domestic violence is already relatively more frequent in families with problem drinking, thus, an increased risk may be anticipated. It is, therefore, highly important to address the risk of domestic violence in therapy. Addressing this risk is mandatory in the interventions and includes developing safety plans together with the CSO. It is, however, important to bear in mind that the risk of abuse and suffering, on the part of the CSOs, is even higher if the problem drinking continues unaddressed. We expect no risks or side-effects for the participants.

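### The one-sided 5% sample-size calculation rests on a no-harm premise that the article contradicts; a two-sided test needs 130 per arm, and 106 gives about 83% power, not 90%

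*Protocol article*

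**What the plan says.** The Power calculation section of the protocol article expects different treatment-entry rates by format: "we expect 40% of CSOs receiving self-help material and 60% of the CSOs receiving either Group CRAFT or Individual CRAFT". It then gives its reason for a one-sided calculation: "the effect of CRAFT is one-sided as the intervention of CRAFT cannot make the situation inferior for either the CSO or the drinker". On that basis it concludes that "106 participants in each group are needed to be able to detect a 20%-point difference". The significance level, power and intracluster correlation behind this figure are given as 5%, 90% and 0.05. After 10% dropout and a further 10% loss to follow-up, it becomes 135 per arm and 405 in total.

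Three other places bear on the premise.

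- **Ethics.** The section says that training relatives in new ways of acting may raise tension at home, and adds: "Domestic violence is already relatively more frequent in families with problem drinking, thus, an increased risk may be anticipated". It makes work on this risk mandatory in the interventions. It also says that the risk is higher still if the drinking is left alone, and it closes by expecting no risks or side-effects.
- **Aim and hypotheses.** The aim is to learn "which of the three interventions (individual, group or self-directed CRAFT) is the most effective". Hypothesis 1 is directional: individual and group CRAFT should each do better than self-directed CRAFT.
- **Statistical analyses.** The section names the models. It gives neither the sidedness of the tests nor a rule for the two comparisons with self-help.

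**The concern.** A one-sided test is defensible when a result in the other direction is impossible or would be treated exactly like no difference. The article claims the first, and claims it for the whole situation of the relative and the drinker. Its own Ethics section does not accept that claim. Nor is the second ground available: the aim lists self-help among the candidates for the best format, so a result in its favour is an answer to the question and not merely a failure to reject.

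Two things are at stake. One is the credibility of the 106 per arm and the 90% power, if they hold only under this premise. The other, if the analysis follows the power calculation, is a more lenient standard for claiming that face-to-face CRAFT is superior.

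**Working it through.** **Inputs.** From Power calculation: p1 = 0.40, p2 = 0.60, difference d = 0.20, alpha 5%, power 90%. From Hypotheses: two face-to-face arms, each set against the same control. Arms are of equal size.

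**1. Reproducing 106.** Two proportions, pooled variance under the null, no continuity correction, no design effect:

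n = [z(alpha)·√(2·0.5·0.5) + z(power)·√(0.4·0.6 + 0.6·0.4)]² / d²

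- One-sided 5%: (1.645·0.7071 + 1.282·0.6928)² / 0.04 = 4.207 / 0.04 = 105.2, so **106**. This matches the article.
- Two-sided 5%: (1.960·0.7071 + 1.282·0.6928)² / 0.04 = 5.170 / 0.04 = 129.3, so **130**.

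Other versions at 90% power do not change the reading. One-sided gives 103 (unpooled), 105.6 (arcsine) or 115 (continuity-corrected). Two-sided gives 127, 129.6 or 140 respectively. No two-sided version at the stated power comes near 106.

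**2. Power of a two-sided test at 106 per arm, before clustering.** Power = Φ[(0.20·√106 − z·0.7071) / 0.6928], with 0.20·√106 = 2.059:

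| Level per comparison | z | Power |
|---|---|---|
| One-sided 5% | 1.645 | 90.2% |
| Two-sided 5% | 1.960 | 83.4% |
| Two-sided 2.5% (Bonferroni for two) | 2.241 | 75.3% |

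**3. Error rate in the favourable direction, if the analysis were one-sided.**

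- One comparison: 5%, against 2.5% for a two-sided 5% test.
- Two comparisons sharing one control, equal arms (correlation 0.5), both nulls true, no adjustment: 1 − P(Z1 < 1.645, Z2 < 1.645) = 0.0878, or 8.8%.
- The like-for-like comparator, two unadjusted two-sided 5% tests: 1 − P(Z1 < 1.960, Z2 < 1.960) = 0.0454, or 4.5%.

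Sidedness therefore roughly doubles the rate whether one comparison or two are counted.

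**4. Clustering, for context only.** Neither 106 nor 130 contains an allowance for the stated ICC of 0.05; that is a separate matter. As an illustration, assume 24 clinics of equal size and 3 × 106 = 318 analysed. That is 13.25 per clinic, a design effect of 1 + 12.25·0.05 = 1.61, and an effective 65.7 per arm. Power is then about 75% one-sided and 63% two-sided.

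**The case against.** The strongest reply is that the article fixes no one-sided analysis. Sidedness appears only in the power calculation, and the statistical analysis plan is not at hand. This stands. A reader might infer that the trial will run two unadjusted one-sided tests with an 8.8% false-claim rate, and that an advantage of self-help could never be declared. The article supports neither as fact. Pooling the face-to-face arms or fixing a testing order would hold the rate at 5%, and a multiplicity rule may properly sit in the analysis plan. Setting 8.8% beside 2.5% would also compare two tests with one; the fair comparator is 4.5%.

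Two further arguments are tempting but weak.

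- The remark that "an open group format may also be negatively affected by a constant influx and outflux of people in the group" (Background, under Craft) belongs to a comparison of open with closed groups. It is not a reason to expect open groups to do worse than the book.
- It might be said that harmless CRAFT would tell us nothing about face-to-face CRAFT against the book, because all arms receive CRAFT. But both face-to-face arms also receive the book. If the sessions truly could not harm, book plus sessions could not be worse than book alone. The weakness lies in the premise, not in that step.

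It is also fair that the Ethics section concerns tension and violence, whereas the powered outcome is treatment entry; that the section regards continued drinking as the greater risk; and that Hypothesis 1 is directional. These points soften the contradiction without removing it. The premise is worded to cover the whole situation of both people, and a directional hypothesis does not by itself justify a one-sided test when the aim includes the opposite result.

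**Conclusion.** The point holds as a fault in what the article states. The reason given for one-sidedness conflicts with the Ethics section and fits poorly with an aim that has no direction. That reason carries the sample size: 106 per arm is the one-sided figure, a two-sided 5% test needs 130, and 106 gives about 83% power per comparison instead of 90%. These figures assume the article's 40% and 60%, equal arms and no clustering.

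The consequence depends on an analysis choice that is not stated. If the analysis is two-sided, the loss is in power. If it is one-sided, the favourable-direction error rate is 5% per comparison, twice the usual 2.5%. The 8.8% overall rate applies only if both comparisons are also tested at that level without adjustment.

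**What to change.** - Delete the sentence that justifies a one-sided effect, and reconcile the no-harm wording with the Ethics section.
- State that individual against self-help and group against self-help are tested two-sided and reported with 95% confidence intervals. If both are confirmatory, Holm or Dunnett is a reasonable way to hold the overall error at 5%.
- Restate power at the planned size on that basis: about 83% per comparison at two-sided 5%, about 75% at the strictest Bonferroni step, both before clustering, and lower once the ICC of 0.05 is applied.
- Settle this before the primary outcome is analysed, since sidedness chosen after seeing results would not be credible.

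The cost is a change of wording and a less favourable stated power. No added participants or data are required. Restoring 90% would be a different decision: 130 / 0.8 = 162.5, so 163 per arm and 489 in total against 405, for a single two-sided 5% comparison and still before clustering.

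### The 106 per arm is the sample size for an individually randomised trial; the stated ICC of 0.05 is not in it, and with 24 clinics power is about 75%, not 90%

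*Protocol article*

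**What the plan says.** The Design section states that "The study is a cluster randomized controlled trial, carried out in public alcohol treatment facilities", and the Abstract says that participants "will be recruited from 24 alcohol outpatient clinics". Under Power calculation the article takes its rates from an earlier small trial: "we expect 40% of CSOs receiving self-help material and 60% of the CSOs receiving either Group CRAFT or Individual CRAFT". It justifies a one-sided test on the ground that "the effect of CRAFT is one-sided as the intervention of CRAFT cannot make the situation inferior". From this it concludes that "106 participants in each group are needed to be able to detect a 20%-point difference", at a 5% α level, with "a power of 90% and an ICC of 0.05". It then allows for about 10% dropout and a further 10% loss to follow-up, which takes 106 to 135 per group and 405 in total.

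**The concern.** In a cluster randomised trial an ICC changes the sample size only through the number of participants per cluster. An ICC of 0.05 with more than a handful of participants per clinic should raise the number well above the individually randomised figure. Here the stated number looks like the individually randomised figure itself.

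What is at stake is the reading of the primary comparison, Hypothesis 1 (face-to-face CRAFT against self-help). The Discussion says that self-help, if it proved equally effective, would be cheap and easy to introduce nationwide. A non-significant result could therefore influence policy, and readers would take it as coming from a trial with only a 10% chance of missing a 20-point difference.

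**Working it through.** **Inputs.** From Power calculation: 40% and 60%, one-sided α 0.05, power 90%, ICC 0.05, 106 evaluable and 135 recruited per arm, 10% + 10% attrition. From the Abstract: 24 clinics (17 at first under Design, plus seven added under Pilot phase). Assumed, because the text does not say: 8 clinics per arm, of equal size, and one face-to-face arm compared with self-help.

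**1. Reproducing 106.** Pooled-variance formula, no clustering:

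n = [1.645 × √(2 × 0.5 × 0.5) + 1.282 × √(0.24 + 0.24)]² / 0.2² = 105.16, rounded up to 106.

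This matches the stated figure exactly. The two-sided version gives 129.3, i.e. 130, already more than 106 before any clustering.

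**2. Could 106 contain the ICC?** The design effect would have to be 106/105.16 = 1.008. With DE = 1 + (m − 1) × 0.05, that means m of about 1.16 participants per clinic. The plan recruits 405/24, or about 17 per clinic.

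**3. Could the step to 135 contain it?** Attrition alone gives 106/0.80 = 132.5 (133) or 106/0.81 = 130.9 (131). That uses up nearly all of the increase.

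**4. Power with the ICC applied.** Analysed per arm: 135 × 0.8 = 108. Per clinic: 108/8 = 13.5. DE = 1 + 12.5 × 0.05 = 1.625. Effective size: 108/1.625 = 66.5 per arm.

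- One-sided: Φ{[0.2 × √66.5 − 1.645 × 0.7071]/√0.48} = Φ(0.67) = 75%.
- Two-sided: the same with 1.960 in place of 1.645 = Φ(0.35) = 64%.

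Using exactly 106 analysed changes little: m = 13.25, DE = 1.6125, effective size 65.7, one-sided power 74.6%.

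**5. Sensitivity** (ICC 0.05 and 108 analysed per arm unless stated):

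| Scenario | Design effect | One-sided power | Two-sided power |
|---|---|---|---|
| 24 equal clinics | 1.63 | 75% | 64% |
| 24 clinics, clinic-size CV 0.6 (illustrative) | 1.87 | 70% | 58% |
| The initial 17 clinics | 1.90 | 69% | 57% |
| 24 equal clinics, all 135 analysed | 1.79 | 79.5% | 69% |
| 24 equal clinics, ICC 0.01 | 1.13 | about 87% | about 80% |

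For unequal clinics, DE = 1 + [(1 + CV²) × m − 1] × ICC = 1 + (1.36 × 13.5 − 1) × 0.05 = 1.87. With 106 analysed, 5 to 9 clinics per arm give one-sided power of 66% to 76%. Using a t reference with 14 degrees of freedom instead of the normal gives about 72% for 8 clinics per arm.

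**6. What 90% would take.** With an effective size of 66.5 per arm and 40% in the control arm, the difference detectable with 90% power is about 25 points one-sided or 28 two-sided. To detect 20 points with 8 clinics per arm, the analysed number would have to be 105.16 × 0.95 / (1 − 105.16 × 0.05/8) = 99.9/0.343, or about 291 per arm.

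**The case against.** The best counter-argument is that Hypothesis 1 can be read as both face-to-face arms pooled against self-help. A 2:1 comparison needs only 79 controls before clustering, and a design effect of 106/79 = 1.34 would bring that to 106, so the ICC might have been used after all. But 1.34 corresponds to about 8 participants per clinic, hence about 13 clinics per arm and 40 in total, against 24. The section also speaks of a number needed in each group. With 24 clinics and ICC 0.05 the pooled comparison reaches about 85% one-sided, still short of 90%. It would reach 90% only if the ICC were about 0.03 (DE = 1 + 12.5 × 0.03 = 1.375; 108/1.375 = 78.5 controls), which is not the stated value.

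Some points stand. How the authors arrived at 106 is inferred from an exact numerical match, not documented. The 75% is one scenario: it assumes equal arms, equal clinics and a pairwise contrast. The section's silence on clinics per arm is not a fault in itself, since the allocation figure is not shown and an article condenses the full protocol. The two-sided figures describe a test the power section does not use, the 17-clinic figures an earlier stage of recruitment, and the CV of 0.6 is illustrative.

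It is also true that the planned mixed-effects logistic regression can account for clinics, so this is not a bias or type I error problem, and that a null result should be judged mainly by its confidence interval. None of this makes the 90% statement correct.

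**Conclusion.** The concern holds: the power statement is wrong as written. The stated inputs yield 106 only when clustering is ignored, and no reading examined gives 90% power at the stated ICC with 24 clinics. On the pairwise comparison with 8 equal clinics per arm and 108 analysed, the type II error for a 20-point difference is about 25% rather than 10%. Fewer or unequal clinics make it worse, and the pooled contrast reduces it only to about 15%. That the ICC has no effect on the 106 follows from the section's own figures and does not depend on how clinics are split; the exact size of the shortfall does. It must be corrected because it concerns the headline power for the primary outcome.

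**What to change.** Keep the 405 participants and rewrite the power statement:

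- Delete the claim of 90% power for 20 points at ICC 0.05.
- State the contrast being powered, the number of clinics per arm and the expected analysed number per clinic. If the split is equal, that is 8 clinics and about 13.5 per clinic.
- Give the design effect (1 + 12.5 × 0.05 = 1.63), the effective size (about 66 per arm) and the resulting power for 40% versus 60%: about 75% at one-sided 5%, or 64% at two-sided 5%.
- Give the difference detectable with 90% power: 25 points one-sided, 28 two-sided.
- Show how power varies over ICC 0.01 to 0.05 and with unequal clinic sizes.

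The cost is a reworded section and a less favourable power figure. No extra participants are needed and trial conduct does not change.
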